##### Among subjects with 3-month PTSD

To describe PTSD complications and comorbidities, we will consider the proportion of patients with excessive alcohol consumption (AUDIT), the proportion of patients with tobacco addiction and its level (low, medium or high; Fagerström test), the severity of depressive symptoms (QIDS) and the proportion of patients in each of the five categories (from no depression to very severe depression), and the response to item 12 of QIDS-SR16 which will depict proportion of subjects with suicidal ideation.

We will use mean, standard deviation, median, and interquartile range to illustrate the number of days lost from work and the number of suicide attempts over the last 3 months. The proportion of patients with at least one of these events will also be measured.

We will present secondary endpoint results for the total study population and the subgroups according to the level of risk identified at inclusion by the IES–R score (moderate risk = IES-R score 12 to 34; high risk = IES-R score > 34).

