### Secondary objectives

The secondary objectives are to measure acute stress, anxiety disorder, and dissociative experiences in patients at inclusion. At 3 months, the incidence of PTSD, its complications and comorbidities will be estimated, as well as the impact of trauma on occupational and psychosocial functioning of the study subjects.

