At inclusion, we will evaluate patient’s social support as a risk factor and at 3-month follow-up as a psychosocial and occupational consequence of the trauma. For this purpose, we will ask his/her return time to the workplace and use the validated French version of the Social Support Questionnaire 6 (SSQ6) [71, 72]. SSQ6 is a 6-item questionnaire that measures two aspects of perceived social support, i.e. availability and satisfaction. Availability is defined as the individual’s estimation of the number of people who can help him/her if required. Satisfaction is defined as the perceived adequacy between the support received and his/her expectations and needs. For each item, the respondent lists the people (max. 9) he/she can count on in the situation described and expresses his/her degree of satisfaction (from 1 to 6) with regard to this support. We then calculate one score for availability (score N, that varies from 0 to 54), and another for satisfaction (score S, that varies from 6 to 36).

For the assessment of alcoholism and nicotine dependence at inclusion and at 3-month follow-up (as PTSD-related complications), we will use Alcohol Use Disorder Identification Test (AUDIT) and Fagerström test, respectively [73, 74].

The AUDIT consists of 10 questions and screens for risky or harmful use of alcohol. It is the reference for detecting alcohol misuse. Men scoring ≥7 and women scoring ≥6 raise the suspicion of alcohol misuse [73, 75].

The Fagerström test is a quick 6-item test that quantifies patient’s level of nicotine dependence [75]. The score ranges from 0 to 10. Dependency is deemed to be null if the score is from 0 to 2, low from 3 to 4, average from 5 to 6, strong from 7 to 8, and very strong from 9 to 10.

In order to assess depression and suicidal ideation (as risk factors at inclusion), and as PTSD-related complications or comorbidities at 3 months, we will use the Quick Inventory of Depressive Symptomatology (Self-Report) (QIDS-SR16). The QIDS-SR16 is a self-administered questionnaire with 16 items describing the 9 symptom domains of DSM-IV associated with depressive feeling [76–78]. The assessment of depression severity is based on the total score as follows: from 1 to 5, absence of depression; from 6 to 10, slight depression; from 11 to 15, moderate depression; from 16 to 20, severe depression; and from 21 to 27, very severe depression. We will also ask for the number of suicide attempts over the last 3 months.

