#### Secondary outcome criteria analysis

In the cross-sectional study subjects, we will analyze the proportion of patients at moderate risk (IES-R score 12 to 34) and at high risk (IES-R score > 34) of PTSD at inclusion and their 95% confidence interval.

In the cohort study population, we will analyze the proportion of subjects with a diagnosis of PTSD at 3 months with its 95% confidence interval.

To describe results of the questionnaires, we will consider total score of PDEQ, STAI-Y (A & B forms), AUDIT, Fagerström, QIDS-SR16 and SSQ6 evaluated at inclusion. To present the results of the questionnaires at 3 months, we will focus on total score of STAI-Y (A & B forms), AUDIT, Fagerström, QIDS-SR16 and SSQ6 evaluated again after 3 months.

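### Complications and comorbidities are described only as 3-month proportions among PTSD cases, so problems associated with PTSD cannot be told from those already present at inclusion

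*Protocol article*

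**What the plan says.** The secondary objectives state that at 3 months "the incidence of PTSD, its complications and comorbidities will be estimated". The analysis sits under the sub-heading "Among subjects with 3-month PTSD" and opens: "To describe PTSD complications and comorbidities, we will consider the proportion of patients with excessive alcohol consumption (AUDIT"). Tobacco addiction by level and the five QIDS-SR16 severity categories follow, then "the response to item 12 of QIDS-SR16 which will depict proportion of subjects with suicidal ideation". The same sub-section summarises "the number of days lost from work and the number of suicide attempts over the last 3 months".

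Its closing sentence names the reporting groups: "We will present secondary endpoint results for the total study population and the subgroups according to the level of risk identified at inclusion". That level is the IES-R category. PTSD status at 3 months is not one of those groups.

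Other parts of the article bear on this:

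- *Secondary outcome criteria* has AUDIT and Fagerström measured "at inclusion and at 3-month follow-up (as PTSD-related complications"). It treats QIDS-SR16 as a risk factor at inclusion and as a complication or comorbidity at 3 months.
- Table 1 has all three instruments at both visits, and Table 2 lists alcohol misuse and smoking among the candidate PTSD risk factors.
- *Secondary outcome criteria analysis* says "we will consider total score of PDEQ, STAI-Y (A & B forms), AUDIT, Fagerström, QIDS-SR16 and SSQ6 evaluated at inclusion", and then takes the same total scores, except PDEQ, again at 3 months.

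**The concern.** The same conditions appear on both sides of PTSD in this plan: as possible predictors at inclusion and as possible consequences at 3 months. If the predictor hypothesis is right, people who go on to have PTSD start with more alcohol, tobacco and depressive problems than those who do not. A raw 3-month proportion among cases then mixes problems carried over from inclusion with problems that appeared afterwards. Without the non-PTSD group beside it, it does not show whether the level is unusual for trauma patients seen in these emergency departments.

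At stake is the reading of a secondary result. The label for AUDIT and Fagerström invites readers to take the figure as something that followed PTSD, and the planned table could not support or refute that.

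**Working it through.** **1. Group sizes, from the article's own figures.** The sample size section assumes 40% PTSD in the unexposed, relative risk 1.4, alpha 0.05 and power 80%. The exposed rate is 0.40 × 1.4 = 0.56. The usual two-sided formula with equal groups and no continuity correction gives, per group,

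n = [1.96 √(2 × 0.48 × 0.52) + 0.8416 √(0.40 × 0.60 + 0.56 × 0.44)]² / 0.16² = 151.9, so 152.

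That is 304 in total against the stated 305, so the figure reproduces. The article then expects 305 × 0.40 = 122 cases, which leaves 305 − 122 = 183 without PTSD.

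**2. What each planned summary provides.**

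| Planned summary | Who | Split by 3-month PTSD? | Linked to own inclusion status? |
|---|---|---|---|
| Complications and comorbidities | PTSD cases | No, cases only | No |
| Total scores at inclusion and at 3 months | Not restricted to cases | No | No |
| Secondary endpoints, total and by IES-R level | Scope unclear; the total contains the cases | No | No |
| Logistic models (primary analysis) | Cohort | Yes, PTSD is the outcome | Inclusion factors predict PTSD, not 3-month alcohol, tobacco or depression status |

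No row gives a PTSD versus non-PTSD contrast at 3 months, or a change within patients.

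**3. How much could be carried over.** The article gives no rate for any of these conditions, so the inputs here are assumptions. Let b be the proportion of the 122 cases positive at inclusion, all remaining positive, and i the proportion of the others who become positive. The 3-month proportion is p = b + (1 − b) × i, and the share of it already present at inclusion is b / p.

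| b | i | p | 3-month positives among 122 | Share present at inclusion |
|---|---|---|---|---|
| 5% | 10% | 14.5% | 18 | 34% |
| 10% | 10% | 19% | 23 | 53% |
| 20% | 5% | 24% | 29 | 83% |
| 20% | 10% | 28% | 34 | 71% |
| 30% | 10% | 37% | 45 | 81% |

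With i = 0 the share is 100% in every row. If some baseline problems resolve, the shares fall. Very different mixtures can lie behind similar 3-month proportions, and the planned analysis shows only p.

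**4. What a comparison could show.** With 122 against 183, two-sided 0.05 and 80% power, the smallest detectable proportion in cases is about 22% against 10%, 35% against 20%, or 46% against 30% in non-cases (comparator rates assumed). For 28% against 20%, the half-width of the unadjusted 95% interval for the difference is 1.96 × √(0.28 × 0.72/122 + 0.20 × 0.80/183) = 0.099. The 8-point difference would thus run from about −2 to 18 points. If the anticipated 30% loss is applied to the 400 selected, 280 remain, with 112 cases and 168 non-cases, and precision is slightly worse.

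**The case against.** Much can be said for the plan, and part of it stands.

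- *Baseline scores are used.* A reader might infer that the plan ignores them. It does not. Total scores are summarised at inclusion and at 3 months without restriction to cases, and inclusion factors are tested against 3-month PTSD. The primary analysis should therefore show whether eventual cases started higher. It does not show, patient by patient, who was newly positive.
- *Non-case figures may be recoverable.* If the total study population in the closing sentence means the whole cohort, non-case counts follow by subtraction. But the sentence sits under the PTSD-only sub-heading, so its scope is unclear, and subtraction gives at best a crude contrast.
- *The text says complications and comorbidities, and the aim is to describe.* A comorbidity may precede PTSD, and no causal test is planned. A reader might infer that earlier problems will be counted as complications, or that the secondary objective goes unanswered. Neither follows: a proportion among cases does estimate comorbidity. What remains is that no rule separates the two terms, and that AUDIT and Fagerström are labelled complications alone.
- *Inclusion is not pre-trauma.* The questionnaires are completed after the trauma, up to 1 month later, so an inclusion score may already reflect it. Adjustment gives status relative to inclusion only, and may remove early effects of the trauma. PTSD and the other conditions are also both assessed at about 3 months, so their order stays unknown. This stands and limits what the fix can claim.
- *Some measures are outside the argument.* Suicide attempts and days lost from work refer to the follow-up period, so carry-over from inclusion is not the issue. Only the missing comparator applies to them.
- *Table layout belongs in an analysis plan.* That is often so, and one may exist. Here, however, the article itself fixes the population, the measures and the reporting groups.

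**Conclusion.** The point holds as a limited weakness in a secondary, descriptive analysis. As stated, the 3-month proportions among PTSD cases cannot distinguish problems associated with PTSD from those already present at inclusion, and the other planned summaries do not close the gap. Under the assumed rates above with 10% new onset, the share already present at inclusion ranges from 34% to 81%. The documents give no rates that would narrow this, so it is an illustration and not an estimate of error. The conclusion itself rests on the stated population and reporting groups and on the dual role given to these conditions, not on the assumed rates.

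The documents do not support the stronger reading that pre-existing illness will be reported as caused by PTSD. The change is worth making because the data are collected in the whole cohort at both times.

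**What to change.** 1. Report AUDIT, Fagerström and QIDS-SR16, including item 12, at 3 months for participants with and without PTSD. Give differences with 95% confidence intervals, adjusted for the same instrument's inclusion score.
2. Add, in each group, the proportion newly above the cut-off among those below it at inclusion. State in advance which Fagerström and QIDS-SR16 category marks the cut-off; the AUDIT cut-offs are already given.
3. Show days lost from work and suicide attempts by PTSD status, without baseline adjustment.
4. Describe the results as comorbidity at 3 months or as associated with PTSD. Say that inclusion scores are taken up to 1 month after the trauma and are not pre-trauma values.
5. State whether the total study population in the closing sentence means the whole cohort or the PTSD cases.

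The cost is a little more analysis, with modest precision as shown above. No new data or participants are needed, and the primary analysis and sample size do not change.

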## Discussion

### Strengths of the study

Firstly, to the best of our knowledge, this will be the first study to assess prevalence of acute stress and risk of PTSD in diverse trauma survivors visiting the ED due to a recent trauma. Previous studies have focused on a specific trauma such as road traffic accidents or rape victims, etc. Secondly, the prospective design of the study will minimize potential information or recall bias. A number of similar studies have used case-control or retrospective designs, and assessed the subjects after months and in some cases after years, which increases the probability of recall bias. Thirdly, the large sample size of this study will ensure the generalizability of the findings. Small sample size is a very common problem in studies on PTSD; some studies have been conducted on a very low sample size while others studies suffer from huge dropout rates that subsequently. Fourthly, we use a holistic biopsychosocial approach to evaluate PTSD predictive factors, while studies investigating PTSD predictors usually explore a single domain (biological, psychological, social, or demographic). Fifthly, the findings will determine PTSD risk in trauma survivors who have an IES-R score between 12 and 34 on, for whom there is no literature on PTSD vulnerability. Sixthly, the use of PCL-5, a standardized scale for diagnosing PTSD at 3 months, is one of the strengths of this study. Specifically trained staff (psychologist, psychiatrist, or intern in psychiatry) will complete the scale during a telephone interview with the consumer. Seventhly, the results will represent a wide geographical area and its innate diversity through the multicenter nature of the study. Finally, the results will provide carers and healthcare providers with invaluable information for the identification of the population at risk of PTSD and to plan preventive screening and therapeutic procedures.

### Challenges

One challenge that we may probably encounter at the cross-sectional stage is that we will not be able to recruit every patient consulting the EDs. Due to their either unwillingness to participate or failure to meet the inclusion criteria. To address this problem, we will elaborate their respective characteristics in contrast to the patients included.

A second potential challenge will be an unexpected rate of dropout in the cohort stage. In order to address this potential issue, selected subjects will receive reminder letters and/or emails 1 month prior to the telephone interview, and we will send them the self-administered questionnaires with a pre-paid return envelope. In addition, a professional will call or email them 15 days in advance to set the date and time of the interview. In case of “no reply”, three more attempts will be made. Finally, the multicenter nature of the study and recruitment capacity of participating EDs (significantly higher than required) ensure feasibility of recruiting expected number of subjects.

## Data Availability

Not applicable.

## Abbreviations

ASD: Acute Stress Disorder
AUDIT: Alcohol Use Disorder Identification Test
CAPS-IV: Clinician Administered PTSD Scale for DSM-IV
ED: Emergency Department
ePRO: electronic Patient Reported Outcomes
IES-R: Impact of Event Scale-Revised
IPV: Intimate Partner Violence
PCL-5: PTSD Check List for DSM-5
PDEQ: Peri-traumatic Dissociative Experiences Questionnaire
PTSD: Post-Traumatic Stress Disorder
QIDS-SR16: 16-item Quick Inventory of Depressive Symptomatology (Self-Report)
SSQ6: 6-item Social Support Questionnaire
STAI-Y (A + B): State-Trait Anxiety Inventory-Y (form A & B)
